### Quality control

ETNA-VTE-Europe will be conducted in accordance with the Guidelines for Good Pharmacoepidemiology Practice (GPP) and the EMA Guideline on Good Pharmacovigilance Practices (GVP) Module VIII (management and reporting of adverse reactions to medicinal products; EMA/813938/2011 rev 1) [16, 17]. Automated checks for plausibility and integrity will be carried out at data entry to permit correction or confirmation by the site. Furthermore, approximately 30% of sites will be randomly selected to undergo on-site monitoring, during which random source data verification will be performed. In particular, monitoring activities will closely assess the completeness and correctness of safety data. Patients with missing observations for a particular time point and/or parameter will be omitted from the corresponding analyses.

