### Objectives and outcome measures

The primary objective of ETNA-VTE-Europe is to quantify the long-term rate of VTE recurrence in a large, real-world population of acute symptomatic VTE patients prescribed edoxaban as part of their initial treatment regimen. Accordingly, the primary outcome measure will be the proportion of such patients who experience recurrent symptomatic VTE on one or more occasions within the 18 months following their index VTE, regardless of the length of edoxaban exposure.

The co-primary objective is to collect and evaluate real-world safety data regarding adverse drug reactions (ADRs) in patients treated with edoxaban across the currently approved indications. Therefore, ETNA-VTE-Europe data will be combined with 18-month safety data from the Edoxaban Treatment in routine cliNical PrActice for patients with non-valvular Atrial Fibrillation in Europe (ETNA-AF-Europe) study, a parallel European PASS evaluating the safety and effectiveness of edoxaban in real-world treatment of atrial fibrillation (AF) [10]. The outcome measure will be the proportion of patients who experience death (all-cause, cardiovascular, and VTE-related), bleeding events (major, clinically relevant non-major [CRNM], and minor bleeding; defined according to International Society on Thrombosis and Haemostasis [ISTH] criteria [11]), hepatic events, and/or other ADRs before the 18 month time-point in the two studies.

Secondary objectives are as follows: to evaluate the effects of persistent edoxaban use and permanent discontinuation on the rate of recurrent symptomatic VTE; to assess the rates of patient-relevant safety outcomes, including bleeding, ischaemic/haemorrhagic stroke, systemic embolic events (SEE), post-thrombotic syndrome (PTS), death, and hospitalisation due to cardiovascular causes; and to characterise the extent of adherence to edoxaban, reasons for and rate of discontinuation. To evaluate the effectiveness and safety of edoxaban relative to other anticoagulants, primary and secondary ETNA-VTE outcome data will be appraised in the context of those from the PREFER in VTE real-world registry and Hokusai-VTE clinical trial [12, 13]. The influence of study setting will also be explored by considering real-world ETNA-VTE data in the context of edoxaban data from the Hokusai-VTE clinical trial [12].

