### Sample size calculations

Assuming an overall 18-month symptomatic VTE recurrence rate [12, 13] of 8.0% in patients who receive edoxaban (regardless of treatment discontinuation) and a relative precision of 15% for a two-sided 95% confidence interval (95% CI), data for 1964 patients will be required to assess with sufficient accuracy the primary outcome. Given an expected dropout rate of 25%, enrolment of 2700 patients should result in an adequate sample size for evaluation at 18 months.

In order to obtain a dataset as large as possible for co-primary outcome assessment, safety data from ETNA-VTE-Europe will be combined with 18-month safety data from ETNA-AF-Europe, a sister European PASS study of edoxaban in approximately 13,100 patients with NVAF [10]. Together, these studies will enrol approximately 15,800 patients, with an overall expected 18-month dropout rate of 20%. Consequently, data for approximately 12,640 patients should be available at 18 months to assess the incidence rates of interest and their 95% CIs. A key aim of this combined analysis is to provide sufficient statistical power to capture uncommon ADRs with low incidence rates; for those that occur at rates of 0.1–1.0%, the corresponding precision of 95% CIs will range from ±0.06% to 0.17%.

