Data will be analysed and presented using descriptive statistics. Categorical variables will be reported as absolute numbers and percentages, and continuous variables will be presented as means with standard deviations or medians with interquartile ranges and minimum/maximum values, alongside the number of missing and non-missing observations. For select variables, 95% CIs will be provided. Where applicable, Kaplan-Meier analysis will be performed to illustrate risk over time. Time-to-event variables will be analysed using Cox proportional hazard regression and presented as hazard ratios with 95% CIs and *p*-values. The type of VTE (DVT only vs. PE ± DVT) will be included in all Cox models as an additional covariate. Based on the results of the Hokusai-VTE and the PREFER in VTE studies [6, 13], no further confounders will be considered at this stage, but any other relevant differences at baseline will be retrospectively added to the model.

A separate analysis combining 18-month safety data from ETNA-VTE-Europe and ETNA-AF-Europe will address the co-primary objective. Data will be presented as absolute and relative frequencies with 95% CIs, overall and for each aforementioned exposure category and subgroup. All statistical analyses will be performed using SAS® version 9.3 or higher (SAS Institute, Cary, NC, USA).

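### Omitting patients with missing observations can bias the primary 18-month recurrence proportion by about its stated precision of ±1.2 points

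*Protocol article*

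**What the plan says.** All references are to the protocol article, Methods.

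- **Objectives and outcome measures:** "the primary outcome measure will be the proportion of such patients who experience recurrent symptomatic VTE on one or more occasions" within 18 months of the index VTE, "regardless of the length of edoxaban exposure". The population is patients prescribed edoxaban as part of initial treatment.
- **Quality control:** "Patients with missing observations for a particular time point and/or parameter will be omitted from the corresponding analyses". No outcome is exempted.
- **Sample size calculations:** "Assuming an overall 18-month symptomatic VTE recurrence rate [12, 13] of 8.0% in patients who receive edoxaban", a relative precision of 15% for a two-sided 95% CI, and 1964 patients with data. Then: "Given an expected dropout rate of 25%, enrolment of 2700 patients should result in an adequate sample size for evaluation at 18 months".
- **Statistical analysis:** "Where applicable, Kaplan-Meier analysis will be performed to illustrate risk over time". Cox models are planned for time-to-event variables and reported as hazard ratios. Neither method is tied to the primary outcome.
- **Documentation and assessment, with Table 1:** the timing of each recurrence is recorded, and death is a documented clinical event. The country-specific last-patient-out questionnaire asks about recurrence only for the time since month 18.

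**The concern.** The outcome definition aims at everyone prescribed edoxaban. The omission rule, read literally, points to a smaller group whose membership depends on what happened during follow-up. With a quarter of patients expected to drop out and no compulsory patient contact, the two can differ materially.

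The rule also does not settle how a patient with partial follow-up counts. Someone with a recurrence at month 3 who is lost at month 6 has a known outcome. Someone event-free at month 6 and then lost does not. Keeping the first and dropping the second leaves every observed event in the numerator but removes event-free follow-up time from the denominator. Dropping both avoids that asymmetry but gives the risk among patients not lost.

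Nothing else in the article cures this. Kaplan-Meier is illustrative and conditional, Cox hazard ratios do not give an 18-month risk, and the last-patient-out query does not look back before month 18. In a single-arm study this absolute risk is the main result, so a shift the size of its confidence half-width matters even though the analysis is descriptive.

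**Working it through.** **Inputs from Sample size calculations:** recurrence p = 0.08; relative precision 15%, so d = 0.15 × 0.08 = 0.012 (1.2 points); dropout 25%; enrolment 2700.

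**1. The plan's own figure.** n = 1.96² × p(1 − p)/d² = 1.96² × 0.08 × 0.92/0.012² ≈ 1963.4 to 1963.5, depending on the rounding of 1.96. Rounded up this is 1964, as stated. Enrolment needed is 1964/0.75 = 2619, below 2700. Expected patients not lost: 2700 × 0.75 = 2025, with half-width 1.96 × √(0.08 × 0.92/2025) = 1.18 points. The sample size is sound.

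**2. Recurrences before dropout kept, event-free dropouts omitted.** Assume constant hazards and dropout independent of recurrence.

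- Cumulative hazards over 18 months: recurrence −ln(0.92) = 0.0834; dropout −ln(0.75) = 0.2877.
- Recurrence observed before dropout: 0.0834/(0.0834 + 0.2877) × (1 − 0.92 × 0.75) = 6.97%.
- Event-free with full follow-up: 0.92 × 0.75 = 69.0%.
- Reported proportion: 6.97/(6.97 + 69.0) = **9.17%**, a bias of about +1.2 points with no informative dropout at all.

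Simulation with other timing patterns (true risk 8.0%, 25% independent dropout):

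| Recurrence timing | Dropout timing | Reported proportion |
|---|---|---|
| constant | front-loaded | 8.79% |
| constant | constant | 9.17% |
| constant | back-loaded | 9.56% |
| front-loaded | front-loaded | 9.18% |
| front-loaded | constant | 9.55% |
| front-loaded | back-loaded | 9.94% |

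**3. All dropouts omitted.** Let RR be the dropouts' recurrence risk relative to completers. Completers' risk = 0.08/(0.75 + 0.25 × RR). The document gives no RR, so the values are assumptions.

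| RR | Completers' risk | Bias (points) |
|---|---|---|
| 0.5 | 9.14% | +1.14 |
| 1 | 8.00% | 0 |
| 1.25 | 7.53% | −0.47 |
| 1.5 | 7.11% | −0.89 |
| 1.7 | 6.81% | −1.19 |
| 2 | 6.40% | −1.60 |

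The bias equals −1.2 points when 0.08/0.068 = 0.75 + 0.25 × RR, that is RR = 1.71 (dropouts 11.6%, completers 6.8%). It equals +1.2 points at RR = 0.48.

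**4. Deaths alone.** No death rate is given. If 2% to 5% of patients died and were omitted, and their recurrence risk were 0 to 3 times that of the others, the shift would be about −0.7 to +0.4 points. At 10% it would be −1.3 to +0.9.

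**The case against.** The strongest reply is that the bias is not inevitable. If every dropout is omitted and loss is unrelated to recurrence, the estimate is unbiased, and the sign in the informative case depends on which group has the higher risk. That stands, so the point is that the rule can bias the estimate, not that it must.

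A second reply is that the article condenses a fuller protocol, and that Kaplan-Meier and Cox models, which use partial follow-up, are not excluded. This also stands in part. Silence on estimator details would be no finding. But the article does more than stay silent: it states a general omission rule that does not suit its own primary outcome, and gives Kaplan-Meier only an illustrative role.

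Four stronger readings might be inferred, and the document does not support them:

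- **All early deaths are removed.** The rule covers missing observations. Death is a recorded event and part of the co-primary outcome. What the article leaves open is how deaths count in the recurrence proportion.
- **Patients with a documented recurrence who later die necessarily leave the analysis.** Their outcome is already known, and the text does not say they are dropped.
- **The step from 2700 to 1964 patients proves a completers-only analysis.** Inflating enrolment for dropout is routine under any estimator.
- **Dropouts are counted as event-free.** That would contradict the stated rule.

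**Conclusion.** The concern holds as a should-fix. The stated rule, applied literally to the 18-month proportion with 25% dropout, can shift the primary estimate by about the 1.2-point half-width for which the study was sized. This happens without informative dropout if pre-dropout recurrences are kept and event-free dropouts removed: about 9.2% under constant hazards, 8.8% to 9.9% over the timing patterns tried. If all dropouts are removed, it requires their risk to be about 1.7 times the completers' risk, or about half of it in the other direction.

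The assumptions are the plan's 8.0% and 25%, the relative risks, the timing patterns and the counting convention; the document does not give the last three. A reader might infer that the reported figure will certainly be biased, or biased downwards, but the document supports neither. The planned numbers of 1964 and 2700 are unaffected.

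**What to change.** Define the primary result as the 18-month cumulative incidence of first adjudicated symptomatic recurrence in all enrolled patients, with a 95% CI. Censor at last documented contact and treat non-VTE death as a competing event. A recurrence documented before dropout then counts, event-free follow-up contributes until it ends, and the role of deaths is explicit.

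Restrict the omission rule under Quality control to descriptive variables such as laboratory values. Add one sensitivity analysis for informative dropout, for example inverse-probability-of-censoring weighting.

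Cost: a wording change and slightly more analysis work. Recurrence timing and death are already collected, and forms are completed after each patient interaction, so no new data or patients are needed.

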### Sample size calculations

Assuming an overall 18-month symptomatic VTE recurrence rate [12, 13] of 8.0% in patients who receive edoxaban (regardless of treatment discontinuation) and a relative precision of 15% for a two-sided 95% confidence interval (95% CI), data for 1964 patients will be required to assess with sufficient accuracy the primary outcome. Given an expected dropout rate of 25%, enrolment of 2700 patients should result in an adequate sample size for evaluation at 18 months.

In order to obtain a dataset as large as possible for co-primary outcome assessment, safety data from ETNA-VTE-Europe will be combined with 18-month safety data from ETNA-AF-Europe, a sister European PASS study of edoxaban in approximately 13,100 patients with NVAF [10]. Together, these studies will enrol approximately 15,800 patients, with an overall expected 18-month dropout rate of 20%. Consequently, data for approximately 12,640 patients should be available at 18 months to assess the incidence rates of interest and their 95% CIs. A key aim of this combined analysis is to provide sufficient statistical power to capture uncommon ADRs with low incidence rates; for those that occur at rates of 0.1–1.0%, the corresponding precision of 95% CIs will range from ±0.06% to 0.17%.

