## Methods

ETNA-VTE-Europe is a single-arm, multinational, prospective, non-interventional PASS, which will be conducted across approximately 310 sites in 8 European countries (Austria, Belgium, Germany, Ireland, Italy, the Netherlands, Switzerland and the United Kingdom). The registry will enrol approximately 2700 patients with acute VTE treated with edoxaban, who will be followed over the 18 months subsequent to the index VTE. Approval from the responsible ethics committees and institutional review boards will be obtained prior to protocol implementation. Informed consent will be obtained from all patients prior to enrolment and compliance with the Declaration of Helsinki will be ensured throughout the study.

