### Site selection

In order to represent the regional distributions of centres, healthcare settings, specialties, and approaches to VTE treatment, a sequential site selection process is underway. This involves identification of potential sites, acquisition of relevant institutional details via a feasibility questionnaire, assessment of suitability, and invitation to participate. To be considered eligible, sites are required to have access to acute VTE patients expected to receive edoxaban treatment, the ability to access the Electronic Data Capture (EDC) system and record data in English, and adequate time and staff to perform all study-related documentation activities. They must also agree to complete a screening log with the aim of maximising the potential for consecutive enrolment, and to perform follow-ups according to routine clinical practice. There is an upper limit of 100 patients per site.

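### The 1964-patient calculation and its 15% relative precision assume independent patients, although enrolment is clustered in about 310 sites; the 15% holds only if the design effect is about 1.03 or less

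*Protocol article*

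**What the plan says.** All places are in the Protocol article.

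- Under Objectives and outcome measures, "the primary outcome measure will be the proportion of such patients who experience recurrent symptomatic VTE on one or more occasions", counted over 18 months whatever the length of edoxaban exposure.
- Sample size calculations assumes an "18-month symptomatic VTE recurrence rate [12, 13] of 8.0% in patients who receive edoxaban" and asks for "a relative precision of 15% for a two-sided 95% confidence interval (95% CI), data for 1964 patients will be required". It then adds: "Given an expected dropout rate of 25%, enrolment of 2700 patients should result in an adequate sample size for evaluation at 18 months". No ICC, design effect or independence condition is mentioned.
- Methods describes the study as one "which will be conducted across approximately 310 sites in 8 European countries", and Site selection adds: "There is an upper limit of 100 patients per site". Sites are chosen to reflect different settings, specialties and approaches to treating VTE.
- Statistical analysis calls the work descriptive and promises 95% intervals for selected variables without naming a method. On the Cox models it says: "The type of VTE (DVT only vs. PE ± DVT) will be included in all Cox models as an additional covariate". On the separate pooled safety analysis with ETNA-AF-Europe it says: "Data will be presented as absolute and relative frequencies with 95% CIs, overall and for each aforementioned exposure category and subgroup".

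**The concern.** Patients at the same site share physicians, referral patterns, follow-up habits and thresholds for investigating symptoms. Follow-up runs according to routine practice and no examination is compulsory, so detection of recurrence may differ between sites. Central adjudication cannot recover an event that a site never found or recorded. If outcomes are positively correlated within sites, 2025 patients carry less information than 2025 independent ones.

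This matters because the study has no comparative test of its primary outcome. The precision of the 18-month recurrence proportion is the only performance property claimed for that outcome, and it is stated without its condition. The pooled safety precision in the same section rests on the same kind of formula.

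**Working it through.** **Inputs from the article.** Recurrence p = 0.08; relative half-width 15%, so 0.15 × 8.0 = 1.20 percentage points; two-sided 95%; 2700 enrolled; 25% dropout; about 310 sites; at most 100 patients per site.

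**Inputs assumed.** ICC (0.01 and 0.05) and the coefficient of variation (CV) of site size (0 and 1). The article gives neither.

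**Step 1: reproduce the plan's figure.** n = 1.96² × p(1 − p) / (0.15p)² = 1.96² × 0.92 / (0.08 × 0.15²) = 1963.5, rounded up to 1964. The match is exact, so the calculation contains no design effect.

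**Step 2: slack at the planned enrolment.** 2700 × 0.75 = 2025 evaluable. The half-width is 1.96 × √(0.08 × 0.92 / 2025) = 1.18 points, or 14.8% of 8.0%. The margin is 2025 − 1964 = 61 patients, and the largest tolerable design effect is 2025 / 1964 = 1.03.

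**Step 3: ICC at which 15% is just met.** Mean evaluable patients per site: m = 2025 / 310 = 6.53. Design effect: DE = 1 + [(1 + CV²)m − 1] × ICC.
- Equal sites: 0.031 / (6.53 − 1) = about 0.006.
- CV 1: 0.031 / (2 × 6.53 − 1) = about 0.003.

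**Step 4: precision and coverage under assumed values.** Relative precision is 14.8% × √DE. Coverage of an interval that ignores clustering is 2Φ(1.96/√DE) − 1.

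| ICC | Site-size CV | DE | Effective N | Half-width (points) | Relative precision | Coverage if clustering is ignored |
|---|---|---|---|---|---|---|
| 0.01 | 0 | 1.055 | 1919 | 1.21 | 15.2% | 94.4% |
| 0.01 | 1 | 1.121 | 1807 | 1.25 | 15.6% | 93.6% |
| 0.05 | 0 | 1.277 | 1586 | 1.34 | 16.7% | 91.7% |
| 0.05 | 1 | 1.603 | 1263 | 1.50 | 18.7% | 87.8% |

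A beta-binomial simulation with 310 sites and 4000 replicates agrees. Ignoring clustering, coverage at CV 0 and 1 was 94.7% and 93.3% at ICC 0.01, and 92.1% and 87.7% at ICC 0.05. With a site-clustered variance it was 94.5–95.2% in the same four scenarios.

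**Step 5: how large is ICC 0.05?** At a mean of 8%, the between-site standard deviation is √(0.08 × 0.92 × 0.05) = 6.1 points. In a beta model the central 95% of true site rates would run from about 0.6% to 23%. That is an upper scenario. At ICC 0.01 the standard deviation is 2.7 points.

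**Step 6: the pooled safety figures.** 15,800 × 0.80 = 12,640. Under independence, 1.96 × √(0.001 × 0.999 / 12,640) = 0.055% and 1.96 × √(0.01 × 0.99 / 12,640) = 0.173%. These match the stated ±0.06% to 0.17%, so this precision is plain binomial too. The site structure of ETNA-AF-Europe is not in the article, so no design effect can be computed there.

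**The case against.** A reader might infer that the primary 95% interval is too narrow and that the 15% will not be delivered. The article does not support either as a fact.

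- **Both depend on unknowns.** With equal sites and an ICC up to about 0.006, 2700 enrolled patients still deliver 15%. The cap of 100 is a ceiling; the mean is 2700 / 310 = 8.7 enrolled per site.
- **No interval method is fixed for the primary outcome.** The sentence on frequencies with 95% CIs belongs to the pooled safety analysis, and the Cox sentence names a covariate without excluding a robust variance. The full protocol and the analysis plan are not shown and may already provide for clustering. The coverage figures therefore apply only if patients are treated as independent.
- **Little shows strong correlation.** All patients are prescribed edoxaban and recurrence is adjudicated by an independent committee. Variety between sites in treatment approach does not by itself establish correlated recurrence.
- **The 15% is a planning target.** Under independence with 2025 patients, a true rate of 7.5% gives 15.3% and 7.0% gives 15.9%, as large a shift as an ICC of 0.01 produces. The analysis is descriptive, and no decision threshold hangs on the primary outcome.

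All of this stands, and it limits the point to a conditional one. It does not remove it, because the anchor is a figure that the article itself states. A clustered analysis would give an honest interval but would not make the 15% true at a design effect above 1.03.

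**Conclusion.** The point holds in conditional form. The 1964 patients and the 15% relative precision assume independence, and the planned enrolment leaves room for a design effect of only about 1.03. Under the assumed ICCs the loss is modest at 0.01 (15.2–15.6% instead of 15%, coverage about 94% if clustering is ignored). It is material at 0.05, the upper scenario (16.7–18.7%, coverage 92–88%). These ranges rest on 310 sites, 2025 evaluable patients, an 8.0% rate, and site sizes between equal and CV 1.

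For the pooled safety proportions, all that can be said is that the stated precision also assumes independence; no magnitude is claimed.

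**What to change.** 1. In Sample size calculations, restate the 15% as the precision under independent patients and add the expected range under assumed ICCs (about 15–19% for ICC 0.01 to 0.05 with site-size CV up to 1).
2. State that the 95% CI for the 18-month recurrence proportion uses a variance clustered on site, for example SAS PROC SURVEYFREQ or SURVEYMEANS with site as cluster and country as stratum.
3. Use a site-robust (sandwich) variance in the Cox models, for example PROC PHREG with COVS(AGGREGATE) and site as the ID variable.
4. Apply the same variance to the pooled ETNA-VTE/ETNA-AF safety proportions where event counts allow.

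If the unseen analysis plan already covers items 2 to 4, only item 1 remains.

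No additional patients are needed, because the stated precision is qualified and the target is not enforced under clustering. The cost is a few sentences and standard options in the SAS software already named. The downside is somewhat wider intervals and a slightly less favourable stated precision.
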